#### Depression and anxiety

Evaluation of depressive symptoms will be performed using Beck Depression Inventory, which consists of an original scale of 21 items, including symptoms and attitudes, whose intensity varies from 0 to 3. Items refer to sadness, pessimism, feeling of failure, lack of satisfaction, sense of guilt, sense of punishment, self-blame, self-accusation, suicidal ideas, bouts of crying, irritability, social withdrawal, indecision, distortion of body image, inhibition to work, sleep disorder, fatigue, loss of appetite, weight loss, somatic concern, decreased libido. The adequacy of the Brazilian version for clinical use was evidenced in the discriminant validity study, in which significant differences of score were obtained in different samples of anxious and depressed patients clinically diagnosed (61). Higher values indicate greater severity of depressive symptoms.

Anxiety will be assessed through the Brazilian version of Beck Anxiety Inventory, which is one of the most widely used instruments to assess anxiety symptoms in clinical and research contexts. Similarly, to the depression inventory, it consists of 21 items that cover the most frequent symptoms of anxiety, with each item scoring from 0 to 3 and the higher the score, the more severe the symptoms (62).

#### Stress

Stress will be evaluated using the Brazilian validated perception stress scale with 10 items (63). The PSS-10 is a general scale in which individuals rate the frequency of their feelings and thoughts related to events and situations that occurred in the last month. Six items are negative (items 1, 2, 3, 6, 9, 10) and the remaining four are positive (items 4, 5, 7, 8). There are five options of answers that ranges from “never” (0) to “often” (4). The four positive items are scored inversely. The final score is obtained summing up the scores from all items, with higher scores corresponding to greater stress.

#### Sleep quality

Sleep quality will be assessed using the Brazilian version of Pittsburgh Sleep Quality Index (64). This questionnaire is composed of 19 questions divided into 7 components (subjective quality of sleep, sleep latency, duration of sleep, habitual sleep efficiency, sleep changes, use of sleeping drugs, and diurnal sleep dysfunction). Each component has a score that ranges from 0 to 3 and an overall score that ranges from 0 to 21 according to the sum of each component. Higher scores indicate worse sleep quality. A cutoff point greater than 5 has been used to indicate poor sleep quality.

#### Medication use, adherence, and adverse drug events

Information on quantity and dosage of the medications regularly used will be obtained from patient’s medical records using the closest medical appointment to the study assessment. Medication adherence will be assessed using the Brazilian version of Medication Adherence Rating Scale (MARS). This questionnaire comprised 10 dichotomous questions (yes/no) to assess intentional (“I avoid using it if I can”) and non-intentional medication adherence (“I forget to use it”). The answers are scored as zero (non-adherence) or one (adherence) and a global score is obtained by summing the items values, so that the result ranges from 0 (low probability of adherence) to 10 (high probability of adherence) (65, 66). The incidence, cause, and intensity of adverse drug events (ADEs) will be determined during the study follow-up based on the information contained in medical records. The Naranjo algorithm and intensity classification will be applied to determine the cause and intensity of ADEs (67).

#### Biochemical, inflammatory, and cardiac biomarkers

Blood drawn will be performed at the INI-Fiocruz laboratory, after at least 10-h overnight fast. Complete blood counts, lipid profile, glucose, insulin, urea, creatinine, lactate, uric acid, glycated hemoglobin, sodium, potassium, chlorine, calcium and magnesium will be evaluated. The inflammatory markers that will be analyzed are C-reactive protein, tumor necrosis factor, interleukin β-1, interleukin-6, interleukin-10, interleukin-17, MCP-1, MMP-2, MMP-8, MMP-9, PIIINP, CTx, sST2. Biomarkers of cardiac function and fibrosis such as BNP, troponin and galactin-3 will also be evaluated.

The plasma lipids will be measured using Kit Gold analyzes, the exception of LDL and VLDL cholesterol that will be estimated by the Friedwald formula (68). Plasma glucose will be determined by enzymatic-colorimetric assay (Kit Gold analyzes), using Konelab 6.0.1, with automated reading at a wavelength of 500 nm. Plasma insulin will be determined by radioimmunoassay (Immuchem Kit 125/RIA). The following formula will be used to calculate HOMA-IR: HOMA-IR = fasting glucose (mmol/l) X insulin (μU/ml)/22.5. Inflammatory and cardiac biomarkers will be dosed using specific kits using the Elisa method. For analysis of biomarkers that are not included in the INI/FIOCRUZ exam routine (inflammatory and cardiac biomarkers), the blood samples will be centrifuged and then stored at −70°C until the time of laboratory analysis, remaining stored under the responsibility of the principal investigator of this research project ([name]).

### Participant timeline

Time schedule of enrollment, interventions, assessments and visits for participants is presented in Figure 1.

**FIGURE 1 F1:**
[figure not shown]
SPIRIT schedule of enrolment, interventions, and assessments of the study.

### Masking

Since home-based exercise implies a behavioral intervention, it is not feasible to mask the patients. However, the evaluators and data analyst will be masked. A blinded researcher will perform all data analysis.

### Intervention

Participants in the intervention group will undergo a home-based exercise program whilst those in the control group will receive only general information regarding the benefits of physical activity. The intervention group will receive a booklet with routines of physical exercises (Supplementary Appendix 1) to be performed at home three times a week, 60 min per session. The physical exercise program will be divided into three parts: (1) warm-up (5 min): stretching exercises and joint mobilization; (2) aerobic activities (20 to 40 min): circuit exercises involving large arm and legs muscle groups, as well as exercises using ball, calisthenics exercises and standing up from a chair (balls will be provided); (3) cool-down (5 min): the same stretching exercises from the warming-up period. The participants will be encouraged to perform aerobic activities with moderate intensity, characterized by a mild breathing discomfort that allows talking during the exercise (69). In the first week, a duration of approximately 20 min for aerobic activities will be recommended, with a 10 min weekly increments, until the duration of 60 min for the overall training session is reached. Patients will be advised to reduce training intensity if they experience any discomfort during exercise such as shortness of breath and/or muscle pain. The exercise routine will be modified after 3 months of follow-up, when a booklet with new exercises will be delivered to patients (Supplementary Appendix 2). For participants that have a mobile phone, messages with animated GIFs will also be send to facilitate the understanding of the exercises to be performed.^1^

Adherence to the exercise protocol will be verified by recording the activity at the end of exercise booklet and during the periodic visits to INI-Fiocruz. Additionally, the level of physical activity will be assessed using triaxial accelerometers (Actical, Phillips, Respironics, OR, USA) at baseline and after 6 months of follow-up (70). The accelerometer will be positioned on the non-dominant wrist using elastic wristbands, which must be used for 7 days without interruption, except for water activities and while bathing. Participants will be instructed to maintain their routine (71).

Both groups (intervention and control) will receive the same general nutritional counseling consisting of general orientations about healthy eating habits, such as reducing saturated fat and increasing poly- and monounsaturated fatty acids consumption, increasing water, vitamins and high-fiber carbohydrates consumption, reducing the sodium intake. Nutritional counseling will take place during the assessment visits at baseline, after three and 6 months of follow-up. Compliance to nutritional counseling will be checked using a 24-h recall at baseline and after 6 months of follow-up, consisting on the identification and quantification of all food and beverages consumed in the day before the interview (72). The consumption of nutrients will be calculated using DietWin Professional Version 2008 software.

### Sample size

The sample size was calculated based on the findings by Carta et al. (73), which evaluated the effect of a physical exercise program on the QoL. In this study, there was a difference of 2.2 (± 2.1) points for the intervention group and 0.0 (± 3.2) point for the control group in the physical domain of the WHOQOL-Bref questionnaire (46). Assuming α = 0.05 and β = 0.10 and inflating the sample by 20% for eventual losses to follow-up, a total of 80 individuals will be necessary to perform the present study (40 in each group).

### Interim analysis and stopping rules

Two interim analyses are planned. The first will be conducted when the 40th participant completes 3 months of follow-up and the second when the last recruited participant completes 3 months of follow-up. Trial interruption for ethical reasons due to either positive or negative results exceeding expectations may be recommended by an independent committee. The prespecified stopping rules are >100% difference between group in any outcome, serious adverse events twice as frequent in one of the groups including death, Chagas cardiomyopathy progression, acute myocardial infarction, unstable angina, cardiac arrest, incident HF, and stroke. All these estimates should have a significance level <0.01 in any of the interim analyses.

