### Statistical analysis

A dataset will be prepared including the information from all patients using the Redcap platform. Statistical analysis will be performed using Stata statistical software (version 13.0). The data analysis will comprise the estimation of the mean (standard deviations) for continuous and absolute frequency (percentages) for categorical variables. The effect of the home-based exercise program on the continuous variables over the intervention period will be determined using a linear mixed model. For categorical variables, generalized estimated equations with log link and binomial distribution will be performed to evaluate changes in the proportion of individuals between groups over the time. All measures performed in the intervention and control group will be used, regardless of losses to follow-up or compliance to the protocol during the intervention period, characterizing an intention-to-treat analysis. The variable of interest will be the interaction between time × treatment, which estimates the change rate of the outcome over time. Protocol analysis including only completers will also be performed. Adjustments for baseline prognostic variables will be made in case of unbalance distributions between the groups. A *p*-value < 0.05 will be considered significant for all statistical tests.

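### The interim rule allows stopping on a >100% difference in any outcome at p<0.01, but it defines no scale for the percentage, is not limited to the primary outcome and has no multiplicity control

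*Protocol article*

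**What the plan says.** All the interim provisions are in the protocol article, section Interim analysis and stopping rules.

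- **Looks.** "Two interim analyses are planned". The timing is: "The first will be conducted when the 40th participant completes 3 months of follow-up and the second when the last recruited participant completes 3 months". With 80 participants allocated 1:1, that means about 20 per arm and then up to 40 per arm.
- **Criterion.** "The prespecified stopping rules are >100% difference between group in any outcome". A second criterion concerns serious adverse events.
- **Significance.** "All these estimates should have a significance level <0.01 in any of the interim analyses". The size condition and the p-value condition must therefore both be met.
- **Status.** "Trial interruption for ethical reasons due to either positive or negative results exceeding expectations may be recommended by an independent committee". The rule is advisory and works in both directions.

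Three other sections bear on it. Sample size gives a planning change in the WHOQOL-Bref physical domain of 2.2 (SD 2.1) with exercise against "0.0 (± 3.2) point for the control group". Outcomes names QoL as primary, lists a dozen secondary headings, and takes echocardiogram and fasting bloods only at baseline and 6 months. Statistical analysis says that p<0.05 "will be considered significant for all statistical tests", with no reference to the interim looks.

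**The concern.** A committee needs a rule that it can apply before it has seen which reading favours which decision. This one leaves open what the percentage is a percentage of, and the answer changes how it behaves:

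- Read on levels, it asks one arm's mean to be more than twice the other's.
- Read on changes, it divides by a control change that the protocol itself plans to be zero.

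Because any outcome counts, a chance result in one secondary variable, with about 20 participants per arm, can meet the rule as written. The trial could then be cut short before the 6-month primary question is answered.

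The timing adds to this. The second look takes place "the second when the last recruited participant completes 3 months of follow-up". Nobody is left to enrol by then, so stopping for benefit mainly removes 6-month data.

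**Working it through.** **Inputs from the protocol.** Two looks at 3 months, 20 then 40 per arm; p<0.01 at each look; final test at 0.05; QoL domain scores 1-5; planning changes 2.2 (SD 2.1) and 0.0 (SD 3.2); 80 participants.

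**Assumptions, because the protocol gives no figure.** Tests are two-sided. Between 20 and 39 outcome variables are available at 3 months; 39 is a count of the individual variables in the outcome sections from Blood pressure to Medication use, and the protocol states no total. Between-outcome correlation is 0 to 0.5. Coefficients of variation (CV) are 0.5 to 1.5. There is no dropout at the looks.

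**1. The plan's own figure.** Pooled SD = √[(2.1² + 3.2²)/2] = 2.706. Per arm, n = 2 × (1.960 + 1.282)² × 2.706² / 2.2² = 31.8, so 32. Then 32/0.80 = 40 per arm, 80 in total. The stated sample size reproduces.

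**2. QoL on levels.** The maximum is 5, so a mean more than double the other needs the lower mean to be below 5/2 = 2.5. From 2.5 upwards it is impossible, and below that it needs an extreme separation.

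**3. QoL on changes.** The percentage difference is (2.2 − 0.0)/0.0, which is undefined. If the observed control change, which scatters around 0, is used as denominator, the size condition is met almost automatically. Under the planning values, and assuming the full effect is present at 3 months, the joint rule fires in about 46% of trials at 20 per arm and 84% at 40 per arm.

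**4. One null outcome, p<0.01 alone.** With nested samples the look-to-look correlation is √(20/40) = 0.71. The chance of p<0.01 at either look is then about 1.8%.

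**5. Adding the >100% condition, change scale.** The condition is |difference| > |control change|. The share of p<0.01 results that also pass it is:

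| True change in both arms | 20 per arm | 40 per arm |
|---|---|---|
| 0 | 0.00976/0.00979 = 99.7% | 0.00985/0.00988 = 99.7% |
| 0.5 SD | 0.00705/0.01013 = 70% | 0.00546/0.01019 = 54% |
| 1 SD | 0.00494/0.01003 = 49% | 0.00199/0.00988 = 20% |

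The chance that at least one of m independent null outcomes meets both conditions at either look is 1 − (1 − q)^m, where q is the simulated per-outcome rate:

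| True change in both arms | q | m = 20 | m = 39 |
|---|---|---|---|
| 0 | 1.76% | 30% | 50% |
| 0.5 SD | 1.16% | 21% | 37% |
| 1 SD | 0.59% | 11% | 21% |

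At zero change the size condition filters almost nothing, so correlation can be examined on p<0.01 alone. For between-outcome correlation 0, 0.3 and 0.5, 20 outcomes give about 30%, 25% and 20%, and 39 outcomes give about 50%, 40% and 28-29%.

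**6. Adding the >100% condition, level scale.** The condition is a ratio of means above 2 or below 0.5. A just-significant difference equals 100% of the mean when CV = 1/(t × √(2/n)), which is about 1.17 at 20 per arm and 1.69 at 40. For less variable outcomes the size condition is the binding one. Simulated per-outcome rates over both looks (lognormal and gamma data) are:

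| CV | q | 10 outcomes | 20 outcomes |
|---|---|---|---|
| 0.5 | about 0% | about 0% | about 0% |
| 0.75 | 0.13-0.27% | 1-3% | 3-5% |
| 1 | 0.46-0.80% | 5-8% | 9-15% |
| 1.5 | 0.75-1.18% | 7-11% | 14-21% |

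**7. Final error rate.** If the rule can be used on the primary score, testing it at 0.01, 0.01 and 0.05 gives an overall type I error of about 0.056-0.062, depending on the assumed correlations between looks.

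**The case against.** **The rule is advisory, two-directional and has two conditions.** This stands. The percentages above are chances of crossing a threshold, not of ending the trial, and a sensible committee might ignore an isolated marker. Discretion does not repair the rule, though, because the committee is meant to exercise it on prespecified criteria and these have no single meaning.

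**A reader might infer an unconditional false-trigger chance of 25-50%.** The protocol does not support that. Such a figure uses p<0.01 alone. Once the size condition is added, it holds only on the change scale with control changes near zero, and the protocol gives 0.0 for one QoL domain only.

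**A reader might infer that QoL can never trigger the rule.** That is true in practice on levels and false on changes, as step 3 shows. The two strong claims rest on different readings and cannot be joined.

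**A reader might count the laboratory and echocardiographic variables.** They are not taken at 3 months. At an interim look they exist only for participants who have already reached 6 months, so they are left out of the 20 to 39.

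**Stopping at the second look could bring forward the offer of exercise to controls.** The Ethical aspects section foresees that offer at the end of the study if the effect is important. The gain is at most the remaining 3 months for the last recruits, against the loss of 6-month data.

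**A committee charter may define the terms.** None is shown. The protocol nevertheless states the rule as prespecified, and a charter could not give it one meaning without changing it.

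**Conclusion.** The point holds as a defect in a stated rule. The percentage has no scale or denominator, any outcome can trigger it, and no multiplicity control is stated. The chance that at least one null outcome crosses depends on the reading:

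- near 0% on levels for low-variability outcomes (CV up to 0.5);
- about 5-21% on levels for 10 to 20 highly variable outcomes (CV 1 to 1.5);
- about 20-50% on changes for 20 to 39 outcomes, with control change near 0 and correlation 0.5 down to 0;
- about 11-21% on changes if both arms change by 1 SD and outcomes are independent.

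The outcome counts, correlations, CVs and two-sided tests are assumptions. That one undefined term moves the result across this range is itself the problem. The inflation of the final error rate to about 0.056-0.062 is minor, and it arises only if the rule can operate on the primary score. The placing of the second look follows directly from the text and needs no assumption.

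**What to change.** Change the interim section as follows.

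1. Delete the any-outcome >100% criterion as a ground for stopping for benefit.
2. Consider early stopping for benefit only on one named primary QoL score, at the first interim only, with a stringent boundary such as Haybittle-Peto (two-sided p<0.001). The final test can stay at 0.05, since the overall error is at most 0.001 + 0.05 = 0.051. The physical domain used for the sample size is one candidate. The protocol names only QoL as primary, so the sponsor has to make that choice.
3. Drop the test for benefit at the second interim.
4. Report secondary outcomes to the committee descriptively.
5. Keep the review of harm and serious adverse events as a separate matter for the committee. The present criterion also covers negative results, so deleting it for benefit must not remove that review unnoticed.

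The cost is wording in the protocol and any committee charter, and a smaller chance of stopping early for benefit in a trial of 80 people with 6 months of follow-up. The exact boundary is a design choice. What is needed is a defined score, scale, look and threshold.

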Approximately 50–70% of individuals with chronic CD present the indeterminate form of the disease, characterized by parasitological and/or serological evidence of *T. cruzi* infection, but absence of major clinical signs and symptoms, normal electrocardiogram, and normal chest, esophagus and colon X-rays (7, 8). However, the indeterminate form can progress to the determinate forms of CD, with an estimated annual progression rate of 1.9% (9, 10). Most infected individuals will remain in the indeterminate form for the rest of their life, with a benign prognosis (4, 11, 12). However, subclinical abnormalities have also been observed in patients with indeterminate form of CD in comparison to those without CD, including early cardiac abnormalities (e.g., greater fibrosis mass) (13, 14), changes in biomarkers of the inflammatory profile and cardiac function (15–17), and alterations of autonomic modulation (18–21). The prognostic value of most of these early subclinical abnormalities is still not determined, although a recent study that evaluated parameters derived from two-dimensional strain provided independent predictors progression to Chagas cardiomyopathy in patients with the indeterminate form of CD (10).

Considering that CD is a neglected disease, more prevalent among people with low socioeconomic status, individuals with CD are usually impacted on their personal and professional life since they are frequently labeled as vulnerable and limited in several aspects, making social insertion difficult, and impacting their mental health and physical and psychological domains of quality of life (QoL) (22–25). The decrease in QoL is associated with an increase in the symptoms of depression and worsening of the perception of health (26, 27). Few studies have evaluated impact of CD on mental health, mostly focusing on cardiac and digestive forms, usually excluding participants with indeterminate form of CD. Thus, comprehensive interventions to improve different parameters of the physical and mental health of individuals with indeterminate form of CD are necessary.

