### Outcomes

Participants will be assessed at baseline, and after three and 6 months of follow-up for all variables, except for echocardiogram exam and fasting blood tests that will be performed at baseline and after 6 months of follow-up. Two clinic visits within a 4-week period for each time point will be performed. The first clinic visit will consist of a clinical interview and physical examination, echocardiogram exam, fatigability evaluation, and cardiopulmonary exercise test. The second clinic visit will include fasting blood tests, nutritional interview, physical fitness evaluation, autonomic modulation assessment, and questionnaires to evaluate back pain, QoL, depression and anxiety, and sleep quality.

The primary outcome will be QoL. Secondary outcomes will include blood pressure, physical fitness components, nutritional status, fatigability, autonomic function, cardiac morphology and function, low back pain, depression and anxiety, stress, sleep quality, medication use and adherence, and biochemical, inflammatory, and cardiac biomarkers.

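### Requiring p<0.01 for the safety stopping criterion makes it very insensitive to a real doubling of serious adverse events in an 80-patient trial

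*Protocol article*

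**What the plan says.** The section on interim analysis and stopping rules plans two looks. "The first will be conducted when the 40th participant completes 3 months of follow-up" fixes the first, and the second comes when the last person recruited has reached the same point. An independent committee may recommend interruption. Two kinds of trigger are prespecified: a between-group difference above 100% in any outcome, and "serious adverse events twice as frequent in one of the groups including death, Chagas cardiomyopathy progression, acute myocardial infarction", followed by further cardiovascular events. The section closes with "All these estimates should have a significance level <0.01 in any of the interim analyses". Read naturally, that sentence covers both kinds of trigger. The section gives no safety trigger that is free of it.

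The sample size section sets the trial at 80 participants, 40 per group, and the randomization section states 1:1 allocation.

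**The concern.** A criterion worded as a doubling suggests that the committee will be alerted when one arm has about twice as many serious events as the other. The added significance condition changes that. Serious events are normally few in a trial of this size, and a test at the 0.01 level on small counts passes only for extreme splits. What is at stake is whether the written safety guideline can draw the committee's attention to a real excess of serious events while the trial is still running.

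**Working it through.** **Inputs from the protocol.** Change in the physical domain 2.2 (SD 2.1) v 0.0 (SD 3.2), α = 0.05, β = 0.10, 20% inflation and 80 participants in total (sample size section); 1:1 allocation (randomization section); looks at the 40th and the last participant's 3-month point, and p<0.01 (interim analysis section).

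**Assumptions.** The test, its sidedness and the unit counted are not stated. I use a two-sided Fisher exact test on participants with at least one serious event. The protocol gives no serious-event rates, so the risks in step 4 are mine.

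**1. The plan's own figure.** Per arm n = (1.960 + 1.282)² × (2.1² + 3.2²) / 2.2² = 10.51 × 14.65 / 4.84 = 31.8, rounded up to 32. Then 32 / (1 − 0.20) = 40 per arm, 80 in total. This matches the protocol. The looks therefore have about 20 per arm, then at most 40 per arm (32 per arm if 20% are lost).

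**2. Smallest split with p<0.01.** For a events against 0 with N per arm, the two-sided Fisher p is 2 × C(N, a) / C(2N, a).

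- N = 20: 6 v 0 gives 2 × 38,760 / 3,838,380 = 0.0202; 7 v 0 gives 2 × 77,520 / 18,643,560 = 0.0083. So 7 v 0 is needed, which is 35% of an arm.
- N = 40: 7 v 0 gives 0.0117; 8 v 0 gives 2 × 76,904,685 / 28,987,537,150 = 0.0053. So 8 v 0 is needed, which is 20% of an arm.
- N = 32: 8 v 0 is needed (p = 0.0048).

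Zero events in the other arm is the most favourable case:

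| Events in the other arm | Needed at 20 per arm | Needed at 40 per arm |
|---|---|---|
| 0 | 7 (p = 0.0083) | 8 (p = 0.0053) |
| 1 | 9 (p = 0.0084) | 10 (p = 0.0069) |
| 2 | 11 (p = 0.0057) | 12 (p = 0.0064) |

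Four against none gives p = 0.106 at 20 per arm and 0.116 at 40; five against none gives 0.047 and 0.055. None of these meets the rule.

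**3. An observed ratio of exactly two.** At 20 per arm, 16 v 8 gives p = 0.0225 and 18 v 9 gives 0.0057. At 40 per arm, 24 v 12 gives 0.0129 and 26 v 13 gives 0.0069. An exact doubling therefore satisfies the rule only when at least 90% v 45% (first look) or 65% v 32.5% (second look) of participants have an event.

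**4. Chance of meeting the rule.** I summed the product of the two binomial probabilities over all tables with a ratio of at least 2 in either direction and Fisher p<0.01, for each look separately:

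| Assumed risks | 20 per arm | 40 per arm |
|---|---|---|
| 10% v 5% | 0.1% | 0.7% |
| 20% v 10% | 1.3% | 4.4% |
| 20% v 5% | 3.5% | 17% |

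**5. Does the choice of test matter?** Events needed against zero, first look then second:

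- one-sided Fisher: 7, 7
- chi-square without continuity correction: 6, 7
- chi-square with correction: 8, 8
- Boschloo: 6, 7
- Barnard: 6, 9
- binomial test conditional on the total: 7 one-sided or 8 two-sided, at both looks
- likelihood ratio: 5, 5, but unreliable with an empty cell

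Most fall between 6 and 8, so the conclusion does not hang on Fisher's test.

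**The case against.** The best defence is that the rule is advisory. Interruption may be recommended by an independent committee, and nothing in the section forbids it from acting on fewer events. The article is also condensed, and a full protocol or charter may already provide for review of individual serious events. Both points stand, and they limit the claim to the written guideline. They do not remove it: the article states the significance condition outright, so the point concerns a stated rule and not an omitted detail.

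It is also fair that the event rates are assumed, that the test is unnamed, and that more than 40 people may have been randomised by the first look. That last point would move the first threshold from 7 towards 8 and not lower it.

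A reader might infer more than the document supports:

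- **That a doubling can never reach p<0.01.** It can, at 18 v 9 of 20 or 26 v 13 of 40, though only at very high event rates.
- **That the two conditions contradict each other.** A ratio of at least two together with p<0.01 is a coherent joint rule. Its fault is insensitivity.
- **That progression cannot be seen at the looks because echocardiograms are done only at baseline and 6 months.** ECG abnormalities also define cardiac disease under the inclusion criteria, and a 12-lead ECG is recorded in the exercise test, which is not among the assessments omitted at 3 months. Participants enrolled early may also have had their 6-month echocardiogram by then.
- **That the 1.9% annual progression rate shows the rule to be empty.** It implies 80 × 0.5 × 0.019 = 0.76 progressions over the trial, but progression is only one of the listed events, and rarity alone does not make a rule wrong.

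**Conclusion.** The point holds in this form: by requiring p<0.01, the protocol makes its stated safety criterion very insensitive to a real doubling of serious events. At least 7 v 0 participants with events are needed at the first look and 8 v 0 at the second. The chance of meeting the rule at a given look is 0.1% to 4.4% for the two true doublings examined. Even a fourfold risk (20% v 5%) would meet it only 3.5% and 17% of the time. The thresholds rest on a two-sided Fisher test, with most alternatives giving 6 to 8, and on counting participants with at least one event. The probabilities rest on assumed risks. The conclusion concerns the guideline as written. It does not show that the committee would fail to act on a smaller imbalance.

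**What to change.** Limit the p<0.01 condition to the outcome (efficacy) criterion. For safety, state that the independent committee reviews the listed serious events by arm, as counts with exact confidence intervals, with no significance requirement. This changes only the statistical condition. Which events or what imbalance should prompt a pause is for the committee and the trial team to decide.

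The cost is about one sentence in the protocol, carried into the committee's charter if there is one. Sample size, visits and data collection are unaffected. The downside is that the safety decision then rests on the committee's judgement and not on a p-value.
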